### Recruitment

The study started to recruit participants in February 2025, and the last measurements for the primary manuscript are expected to be collected by the end of 2026.

Recruitment, interventions and data collection will be performed in the specialised eating disorder clinic of the Faculty of Medicine at Ege University Hospital in Izmir (population approximately 4·5 million), Turkey. Before participants are recruited, we will ensure the implementation of Good Clinical Practice guidelines, the establishment of a functioning clinical research infrastructure and the training of study staff.

Participants will be recruited through four possible pathways: (1) AN patients will be recruited from Ege University Faculty of Medicine Hospital by physicians meeting these patients. Healthy controls will be recruited through (2) announcements on Ege University campuses, (3) local hospitals and (4) online platforms such as Instagram.

Individuals who agree to participate will be contacted by study personnel for further information about the study over the telephone. At that time, an initial assessment for eligibility will be performed. For further eligibility assessments, please see the next heading. For adolescents who cannot be reached over the telephone, parents or legal guardians will be contacted. Potentially eligible participants will be scheduled to a study physician for further eligibility assessment and written informed consent.

### Eligibility

Female individuals of 13–18 years of age who are currently patients at the eating disorder clinic and newly diagnosed with AN according to the Diagnostic and Statistical Manual of Mental Disorders, 5th edition^(58)^, and treatment naïve will be eligible. Healthy control participants will be matched on age, sex and education level with the AN participants. The clinical diagnosis/diagnoses for participants will be validated/ruled out by the Schedule for Affective Disorders and Schizophrenia for School-Age Children – Present and Lifetime version^(59)^. The presence of other exclusion criteria will also be further explored at the clinical visit.The exclusion criteria are as follows:Having one or several chronic medical conditions that may interfere with or hinder participation or affect study outcomes.Use of medications that affect hormone levels or eating behaviours.Having one or several severe psychiatric disorders other than AN (e.g. schizophrenia, major depressive disorder, bipolar disorder).Current drug abuse, pregnancy or potential pregnancy (for AN patients, these conditions are excluded as a part of routine care. For healthy controls, no drug testing will be performed.).High risk of refeeding syndrome or severe complications related to eating disorders.Inability to comply with the nutritional programme of the study.Allergies to foods included in the provided meal content.Cognitive impairments preventing comprehension of the study or the informed consent process.Contraindications for MRI (e.g. pacemaker, prosthesis, claustrophobia)Fasting blood sugar above 6·0 mmol/l on the morning of the study, as this indicates either non-compliance with overnight fasting or pre-diabetes/diabetes.

#### Additional exclusion criterion for healthy controls

(1) Having one or several eating disorders, current or past.

Unexpected findings of biochemical anomalies at baseline (please see ‘Assessments’) will not be considered exclusion criteria, and medical conditions will be referred for appropriate treatment.

Participant inclusion in the study will be determined by a study clinician based on the outlined eligibility criteria. In cases of uncertainty, the principal investigator will make the final decision. Importantly, to maintain impartiality and avoid selective recruitment bias, enrolling clinicians will be masked to future treatment allocations, as randomisation will occur at a later point in time. Participants will receive both oral and written information about the study and will provide written informed consent before inclusion. For participants below 18 years of age, written informed consent will also be obtained from parents or legal guardians. Participation in the study is voluntary, and participants may withdraw at any time without any negative consequences or affected subsequent care. Participants may also choose to withdraw any personal data already collected.

### Randomisation

When an eligible participant has been recruited and consented, they will be scheduled for randomisation at a later timepoint. AN participants will be individually randomised to one of the two study arms with a 1:1 allocation ratio by a computer-generated allocation sequence using permuted blocks. The block sizes will vary randomly between two and four.

Randomisation lists will have been pre-prepared by a separate researcher who is not involved in participant recruitment. Sealed envelopes will contain the study ID for each participant and the meal assigned to that individual (caloric or non-caloric). When a participant is ready to enter the study, a researcher will draw an envelope and prepare the assigned meal for that participant in the evening for consumption the next morning.

Participants with AN will be admitted to the clinic’s open inpatient unit on the evening prior to study participation to ensure a 12-h overnight fast. On the following day, they will receive the specified interventions and undergo the outlined assessments. Once an AN participant has been randomised and completed the study, a matched healthy control participant will be recruited. Recruitment of healthy control participants will be conducted by study personnel who are masked to the randomisation outcomes of the corresponding AN participant. This approach ensures that the allocation of both AN and healthy control participants remains concealed from recruiting researchers and those conducting assessments. Healthy control participants will undergo the same eligibility assessments as AN participants, be assigned their own study ID and share the same allocation as their corresponding AN participant. However, unlike AN participants, healthy control participants will not be admitted overnight.

Codes will be used to increase information confidentiality and participant anonymity, and participant allocation will be performed based on these codes. Randomisation will continue until *n* 36 AN patients and *n* 36 healthy controls have completed the study as per-protocol participants.

The randomisation results will not be revealed to anyone other than the individual preparing the assigned meal. The randomisation step will thus be separated from the patient enrolment process and all the other processes of the study. Through that, participants, study personnel and clinicians delivering any co-interventions will be masked to participants’ allocation and so will outcome-assessors and statistical analysts. Participants will be asked to guess their personal allocation after meal-1 to enable a validation of the blinding integrity.

### Intervention protocol

Depending on their randomisation result, participants will be asked to consume one of two jellies, both composed by a dietitian and prepared by study personnel: one containing 400 kcal and the other calorie-free. Both participants and the person handing out the jelly will be unaware of its caloric content. Participants will be given 15 min to consume the jelly, without forcing them to do so, and the amount consumed will be recorded.

The caloric food used in the study will be prepared using gelatine powder, water, granulated sugar, cinnamon, ginger, turmeric and grated lemon zest. To prepare the mixture, plain gelatine powder and 80 g of granulated sugar are mixed with 100 ml of hot water until a homogeneous consistency is achieved. For flavouring, one teaspoon each of cinnamon, ginger and turmeric, along with the zest of half a lemon, is added. The mixture is then brought to a boil, and after 5 min of boiling, the heat is turned off, and the mixture is left to cool for 15 min. It is then poured into a single-serving container, allowed to cool at room temperature and placed in the refrigerator for 2–3 h to solidify. The final product weighs 250 g.

The ingredients of the calorie-free food are water, agar-agar, two teaspoons of the natural sweetener Stevia, cinnamon, ginger, turmeric, grated lemon zest and lemon juice. As with the preparation of the caloric food, all ingredients are mixed and brought to a boil. After it starts boiling, it is stirred for five more minutes, and once it starts to thicken, the heat is turned off, and the mixture is left to cool for 15 min. The prepared meal is then poured into a single-serving container and refrigerated for 2–3 h until it is ready to be consumed. The final product weighs 250 g.

The ingredients and preparation methods were carefully chosen to ensure that both mixtures have a similar appearance and taste.

Three hours after consuming the first mixture (meal-1), participants will be offered a second meal (meal-2). This meal will always contain calories and consist of a nutritionally balanced, standard oatmeal dish with a distinct taste from the first meal. Participants will be allowed to eat freely, up to a maximum of 500 kcal, to minimise the risk of medical complications such as refeeding syndrome in participants with AN. Participants will have 45 min to complete the meal, and the total amount consumed will be recorded.

Apart from meal-1 and meal-2, any oral intake apart from water will be prohibited during the time of the study.

### Adherence to study protocol

Protocol non-adherence is defined as follows:A participant withdraws their consent, choosing to discontinue the study from the time of randomisation to the end of T_2_ data collection.A participant is discovered to have received the wrong type of meal in meal-1.A participant consumes ≤ 30 % of the food provided in meal-1.A participant eats or drinks anything other than the provided meals and water between T_0_ and T_2_ data collection.A participant refuses or is unable to undergo MRI scanning at T_2_.A participant is unable to adhere to the study schedule.An adverse event occurs that renders continued participation inappropriate. Please see ‘Adverse events and security plan’ for details.

All outcome measures detailed under ‘Assessments’ will be collected from all participants. For the primary analysis, all data from participants adhering to the protocol will be included. For details, see the ‘Statistical Methods’ section.

### Adverse events and security plan

Adverse events (AE) are defined as any undesirable experiences requiring healthcare that occur to a participant during the study, regardless of whether they are related to the study or not. All AE reported spontaneously by participants or their relatives or observed by investigators, study personnel or clinicians will be documented in the electronic case report form. Both AE and serious AE – including those resulting in death, being life-threatening, requiring hospitalisation or involving other significant medical concerns – will be promptly reported to the principal investigator. Serious AE that are assessed as potentially related to the study will be reported to the accredited ethics committee that approved the protocol within 7 d of the responsible researcher becoming aware of the event.

Based on previous studies and unpublished preliminary data, significant deterioration of symptoms during the study is not anticipated. However, for safety purposes, self-report questionnaires collected throughout the study will be reviewed by study personnel who will also monitor participant distress. Patients are expected to become anxious when asked to eat a meal, and regular meal-related symptom fluctuations will not be considered as AE. Any other observed worsening of symptoms or adverse reactions will be addressed in discussions with the participant and, when appropriate, their parents or legal guardians.

As the interventions and assessments are provided as part of the regular healthcare system, all participants are covered under standard patient injury insurance. External independent study monitoring will be performed to ensure that all data storage, handling and analysis procedures comply with ethical guidelines, regulatory requirements, quality standards and protocol.

### Assessments

Pre- and post-meal self-report scales will be administered via a secure online platform accessible only to the research team. Pseudonymised data from these scales, as well as all other assessments, will be stored on a secure server with regular security backups. Biological specimens collected during the study will be coded and stored in coolers in a certified biobank for batchwise analysis after the dataset is complete. Physical records will be stored in locked cabinets with restricted access. The pseudonymisation key will be securely stored in a location that is separate from the data.

Participants’ travel expenses and food and beverage costs will be covered, and this amounts to approximately 20 US dollars. Those who fail to attend scheduled appointments as a part of the study will be reminded via telephone or email. Parents and/or legal guardians may also be contacted. A detailed schedule of enrolment, interventions and assessments is presented in Table 2.

**Table 2. tbl2:** Schedule of enrolment, interventions and assessments Table 2 long description.

	Study period					
	Enrolment			Post-allocation		
Timepoint	T_-1_	T_0_	Allocation	T_1_ (post-meal, 15 min)	T_2_ (1 h)	T_3_ (3 h)
Enrolment						
Eligibility screening	X					
Informed consent	X					
BMI calculation	X					
Allocation			X			
Interventions						
Calorie intake in meal-1			I 	X		
No calorie intake in meal-1			I 	X		
Assessments						
Meal-1 food consumption				X		
Self-report	X	X		X	X	X
Blood sampling		X			X	
Blood pressure and pulse		X			X	
MRI		X			X	
Meal-2 food consumption						X

### Eligibility measures

The medical records of all participants will be analysed to identify comorbidities and other exclusion criteria. The biochemical results that will be available for AN patients include lipid profile (total cholesterol, HDL-cholesterol, LDL-cholesterol and TAG levels), blood glucose level, insulin level, thyroid-stimulating hormone, T4, follicle-stimulating hormone, luteinising hormone, oestradiol, prolactin and C-reactive protein. These parameters are routinely checked on all AN patients. No additional blood tests will be performed to identify exclusion criteria, and for healthy controls, these blood tests will not be performed.

Clinician interviews will be performed to verify the clinical AN diagnosis in patients and to rule out any comorbidity in AN and healthy control participants. The Schedule for Affective Disorders and Schizophrenia for School-Age Children – Present and Lifetime version will be used to complement the clinical interview, and it will be performed by a well-trained psychiatrist used to applying the instrument in practice. The Schedule for Affective Disorders and Schizophrenia for School-Age Children – Present and Lifetime version is a reliable and valid tool for diagnosing psychiatric disorders^(59)^.

### Assessments for description of sample

Body weight and height will be measured at T_-1_ to calculate BMI. At the same time, the participants’ sociodemographic background will be assessed using a brief self-made questionnaire. Additionally, at T_-1_, the following self-rating scales will be collected for screening purposes and description of sample: (1) the Autism Spectrum Screening Questionnaire^(60,61)^, (2) the Childhood Trauma Questionnaire^(62)^, (3) Children’s Depression Inventory^(63)^, (4) the Screen for Child Anxiety Related Disorders^(64)^, (5) the Eating Attitudes Test^(65)^ and (6) the Global Assessment of Functioning scale^(66)^.

### Outcome measures

Outcome measures will be assessed at baseline before randomisation (T_0_), 15 min after meal-1 (T_1_), 1 h after meal-1 (T_2_) and 3 h after meal-1 (T_3_), with some measures collected only at specific timepoints. Details for each outcome measure are provided under their respective subheadings and summarised in Table 2. If a participant misses a scheduled data collection timepoint, the following steps will be taken in sequence: (1) if feasible and meaningful, the data will be collected as soon as the issue is identified; (2) if not, the data point may be recorded as missing, and the participant will continue in the study; or (3) if the participant is deemed no longer relevant to the study, they will be excluded from further follow-up and per-protocol analysis.

#### Primary outcome measure

##### MRI

Resting-state MRI scans will be performed at T_0_ and T_2_. MRI examinations will be conducted using a 3.0 Tesla MRI scanner (Siemens Magnetom Verio, Numaris/4, Syngo MR B17) equipped with a 12-channel head coil. First, structural images will be obtained with axial TSE T2-weighted, coronal 3D-SPACE FLAIR and 3D-MPRAGE sequences. Structural images will be reviewed by an on-site radiologist to identify any brain anomalies or pathologies that would render a potential participant ineligible (e.g. structural abnormalities, lesions). If no pathological findings are detected, imaging will continue with a functional MRI sequence, including 9 min of resting-state functional MRI, where participants will keep their eyes open and look at a fixation cross on screen.

#### Secondary outcome measures

##### Self-report

At T_0_, T_1_, T_2_ and T_3_, psychometric evaluations will be performed on Visual Analogue Scales. The following questions will be used at the appropriate timepoints:How anxious are you about consuming the meal? Response options: I feel no anxiety – I feel very anxious.How often do you feel anxious about eating unfamiliar foods? Response options: I do not feel anxious – I feel very anxious.How hungry do you feel? Response options: I feel full – I feel very hungry.How worried are you about the possibility of gaining weight from consuming the meal? Response options: I feel no anxiety – I feel very anxious.How much do you fear becoming obese? Response options: I do not fear – I fear a lot.How much does the thought of becoming obese affect your eating habits? Response options: It does not affect at all – It affects a lot.How overweight do you feel? Response options: I feel very thin – I feel very overweight.

##### Blood sampling

At T_0_ and T_2_, blood samples will be collected from all participants. At T_0_, participants’ fasting glucose will be measured. Neuroendocrine measurements on blood samples taken at T_0_ will include ghrelin, obestatin, peptide YY, leptin and cortisol hormones. These analyses will be conducted using available kits. At T_2_, the same neuroendocrine parameters will be analysed in blood.

##### Blood pressure and pulse

To evaluate cardiovascular responses, blood pressure and heart rate measurements will be performed using an automatic blood pressure monitor and a pulse oximeter (both Sun Tech Medical) at T_0_ and T_2_.

##### Meal-1 and meal-2 food consumption

Although not strictly considered an outcome, the amount of mixture (in grams) consumed in the meal-1 will be recorded and included as a control variable in the analysis. The amount of food consumed in meal-2 will also be recorded by weighing the plate before and after the meal.

### Statistical methods

#### Analysis plan

Analysis will be conducted once data collection is complete. No interim analyses will be performed. Initially, the quality and completeness of the data will be assessed. If available, missing values will be entered using information from the individual’s original data file. The dataset will be examined for outliers and inconsistencies. For categorical variables, any responses outside the defined categories will be coded as missing. For continuous variables, values outside the acceptable ranges will also be coded as missing. Missing data will not be imputed.

The analyses will be carried out by the investigators and a biostatistician using the latest version of SPSS Statistics (IBM Corp.), R (R-core team) or equivalent statistical software. For the analysis of functional MRI data, additional software tools described below will be used. Data analysts will be blinded to the participants’ allocation. Significance testing will be two-tailed, and statistical uncertainties will be reported as 95 % confidence intervals. All tests will be conducted with a significance level of 0·05.

#### Descriptive statistics

Baseline data and descriptive statistics will be reported using standard measures in accordance with Consolidated Standards of Reporting Trials guidelines, and the baseline characteristics of the included participants will be reported per randomisation group and AN status in a baseline table. The following baseline characteristics will be reported: age (years), AN subtype (by categories), co-morbidity (% yes, by diagnostic categories), smoking (% yes, frequency), country of birth (% Turkey, % first-generation immigrant and % second-generation immigrant – with at least one parent born outside of Turkey). Sex will not be reported as all participants will be of female sex.

#### Patient flow diagram

The flow of participants will be illustrated in a flow diagram according to Consolidated Standards of Reporting Trials recommendations (Figure 1).

**Figure 1. f1:**
[figure not shown]
Flow of participants.

#### Primary analysis

For the statistical analysis of functional neuroimaging data, MATLAB and Statistical Parametric Mapping (SPM12) software will be used to assess brain activity patterns and differences across groups. Connectivity analysis will be performed using the CONN Toolbox to examine the relationships between different brain regions and networks. Neuroimaging data will first undergo pre-processing to ensure the data is suitable for further statistical analysis.

The pre-processing steps that will be performed include the following:Realignment: This is the process of correcting head motion of the participants.Slice-Time Correction: This involves correcting for functional differences between slices acquired every 3 s.Coregistration: Anatomical and functional images are overlaid to determine the anatomical location of activation.Spatial Normalisation: This process accounts for individual brain shapes by normalising anatomical MRI images. The template developed by the Montreal Neurological Institute will be used.Smoothing: This is used to improve image quality and will be performed using a 3D Gaussian kernel (full width at half maximum = 8 mm).

After the pre-processing steps, the data of all participants will be registered to the common Harvard–Oxford Cortical Atlas space. Participant and group-level regression analyses will be performed in this atlas space. Functional connectivity analyses will be performed between regions of the components of the Salience Network, including the anterior insula, dorsal anterior cingulate cortex, temporoparietal junction and hypothalamus. Changes in the topology of networks formed by these four regions, in addition to their functional connectivity with each other, will be analysed using Graph Theory. The changes in the connectivity features of these regions before and after caloric/non-caloric intake will be evaluated using both nodal and global metrics. Significant results obtained will be recalculated using masks transferred back to the participant space. Beta values of the regression analysis will be controlled for type-1 errors with false discovery rate and reported accordingly.

The independent variables of the regression analyses will include (1) type of meal (caloric or non-caloric), (2) AN status (AN or healthy control), (3) AN subtype (restrictive or bulimic type), (4) BMI and (5) duration of AN illness. A random effect for each participant and for each matched set of patient and healthy control will be used to account for within-subject correlations from repeated measurements and dependencies within each matched pair.

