The perturbed response to metabolic signals in AN is associated with altered brain activity^(40–42)^. Genes linked to AN are functionally enriched for expression predominantly in brain neurones^(28,43)^. Neurones in the hypothalamus constitute a major metabolic control hub for caloric intake^(44)^. The hypothalamus has been shown to react differently to both blinded gastric loading with glucose and sucrose tasting in AN^(42,45)^. Feeding reduces the hypothalamic levels of the intracellular metabolites glutamate and glutamine in AN patients. This is paradoxical as feeding instead increases them in normal weight and constitutionally lean individuals^(46)^. Chemogenetic activation of the metabolically regulated agouti-related peptide-expressing neurones in the hypothalamus can ameliorate the development of activity-based anorexia, a mouse model of voluntary self-starvation and other hallmark AN characteristics^(47)^. AN also affects the processing of metabolic stimuli in brain areas critical for reward and emotional regulation, such as the amygdala and ventral striatum, as well as parts of the cortex mediating cognitive aspects of food intake^(41,42,45,48–50)^. Functional connectivity analyses indicate that AN perturbs how different brain areas communicate in response to metabolic fluctuations^(27,42,45,46)^. This effect on how the brain processes metabolic fluctuations by integrating information from metabolic, emotional-motivational and cognitive brain areas is supported by neurocircuit mapping in rodents showing that the decision to eat is not a function of discrete areas but rather their intercommunication^(51)^. Metabolic state affects brain processing of various stimuli in patients with acute AN as well as weight-recovered individuals, indicating that how AN affects the brain response to metabolic fluctuations is part of the core AN pathology and not just a result of weight loss^(40,41,49,50)^.

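### 8 mm smoothing is applied before the connectivity and graph analyses, so the hypothalamic node, a small non-cortical region, would be averaged from data already blended with adjacent tissue

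*Protocol article*

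**What the plan says.** All of the relevant text is in the Primary analysis section of the protocol article, apart from the rationale.

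- **Pre-processing.** The list ends with normalisation to the Montreal Neurological Institute template and then smoothing by a 3D Gaussian kernel ("full width at half maximum = 8 mm").
- **Common space.** Once pre-processing is done, every participant's data are to be "registered to the common Harvard–Oxford Cortical Atlas space". The next sentence adds: "Participant and group-level regression analyses will be performed in this atlas space". No other atlas is named.
- **Regions.** Connectivity is analysed among components of the Salience Network, "including the anterior insula, dorsal anterior cingulate cortex, temporoparietal junction and hypothalamus". The graph analysis uses the same set: "Changes in the topology of networks formed by these four regions".
- **Participant space.** Results that reach significance are then recomputed with masks carried back to each participant's own space.
- **Role of the hypothalamus.** The introduction states: "Neurones in the hypothalamus constitute a major metabolic control hub for caloric intake".

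The article does not say where the hypothalamic mask comes from, or that any region time series is taken from unsmoothed data.

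**The concern.** Smoothing suits voxel-wise maps, where it helps to align participants. It suits a small region of interest poorly. When a region average is taken from smoothed volumes, each voxel already contains a weighted share of what surrounds it. The smaller the region is relative to the kernel, the more of its average comes from outside.

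Of the four regions, the hypothalamus is the small, non-cortical one, and it stands for the metabolic side of the question. The primary objective is to separate the neural response to caloric from that to non-caloric meals, and the introduction treats this structure as the metabolic hub. If its time series is largely a blend with adjacent tissue, two things can go wrong. A real calorie-dependent change in hypothalamic connectivity can be diluted and missed, or a change in neighbouring tissue can be reported as hypothalamic. Graph metrics on a four-region network inherit either error.

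The cortical atlas adds to the difficulty. An atlas that covers cortex cannot itself supply a hypothalamic mask, so the mask must come from a source the article does not name.

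**Working it through.** The plan gives no figure for the effect of smoothing, so there is none to reproduce. The check asks how much of a smoothed region average comes from inside the region.

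**Inputs**
- Kernel: 3D Gaussian, full width at half maximum 8 mm (Primary analysis).
- Regions: four, one of them the hypothalamus (Primary analysis).
- Region size: not in the documents. Assumption: a sphere of radius r = 4, 5 or 6 mm, with other sizes shown for range.
- Extraction from smoothed data: implied by the order of steps, not stated separately.
- One node per region: assumption. The article does not say how left and right are handled.

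**Step 1, kernel width.** σ = 8 / 2.3548 = 3.40 mm.

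**Step 2, in-region share of weight.** For a region R of volume V,

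f = (1/V) ∫_R ∫_R G_σ(x − y) dy dx,

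where G_σ is the Gaussian kernel. For a sphere this becomes

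f(r) = ∫₀^{2r} [1 − 3d/(4r) + d³/(16r³)] · √(2/π) · (d²/σ³) · exp(−d²/2σ²) dd.

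The bracket is the overlap of the sphere with a copy of itself shifted by d. The remainder is the density of the kernel displacement. The share was computed on a 0.5 mm grid; for the 8 mm kernel the integral agrees to within about 0.002.

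| Radius (mm) | Volume (cm³) | Inside share, 8 mm kernel | Inside share, 4 mm kernel |
|---|---|---|---|
| 3 | 0.1 | 12% | 40% |
| 4 | 0.26 | 21% | 52% |
| 5 | 0.5 | 31% | 61% |
| 6 | 0.9 | 39% | 67% |
| 8 | 2.1 | 52% | 75% |

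With the 8 mm kernel the share reaches one half only at a radius of about 7.6 mm, that is (4/3)π × 7.6³ ≈ 1,840 mm³, or about 1.8 cm³.

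**Step 3, sensitivity to shape.** An ellipsoid with semi-axes 3, 4 and 5 mm gives 20%. One with semi-axes 4, 5 and 6 mm gives 30%. These are close to spheres of similar volume.

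**Step 4, reach in the primary analysis.** Four nodes give C(4,2) = 4 × 3 / 2 = 6 pairwise connections. The hypothalamus takes part in 3 of them (50%).

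**Step 5, does the participant-space step help?** It acts only on results that have already passed the significance threshold in the smoothed, common-space analysis. A hypothalamic effect diluted below that threshold never reaches it.

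**The case against.** The strongest reply is that the article leaves these details open and does not fix them wrongly. It has four parts.

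1. *Atlas space may mean coordinates only.* The text says that data are registered to, and analysed in, that space. It does not say that the four regions are its labelled parcels. This stands. A reader might infer that every region is taken from the cortical atlas labels and that the hypothalamic node is therefore undefined. The text does not establish either. Masks are mentioned, and a mask in standard space can come from any source.

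2. *An article need not name its mask sources.* This also largely stands. An unnamed mask is mainly missing detail that a fuller document may supply. The Discussion openly says that the analysis plan is loose and that parallel experiments will inform the choice of regions. The missing source is therefore not the main point here.

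3. *The extraction setting is not stated.* One pre-processing list serves both the SPM12 and the CONN analyses, and the team may intend to take region signals from unsmoothed volumes. That is possible, but nothing says so. The stated sequence runs from smoothing to registration to connectivity, and a reader who follows it would use smoothed data. The order of steps is something the article does fix.

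4. *The percentages are not measured signal.* Correct. They are kernel weights for an assumed size, and they ignore differences in signal variance and correlation between tissues. A reader might infer that 61% to 79% of the hypothalamic signal belongs to its neighbours. The calculation supports that statement for kernel weight only.

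**Conclusion.** The point holds as a flaw in the order of processing. Followed as written, the connectivity and graph analyses use data smoothed at 8 mm, and the hypothalamic average is then built mostly from weight outside the region: about 21% to 39% inside for an assumed radius of 4 to 6 mm, and under half for any roughly spherical region smaller than about 1.8 cm³. With one node per region, half of the pairwise connections are exposed.

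The conclusion rests on three assumptions: the size and compact shape of the region, extraction from the smoothed volumes as the sequence implies, and one node per region. It does not rest on the atlas label. That the only named atlas is cortical shows that the hypothalamic mask needs another source, not that the node cannot be defined. The change is worth making because it is nearly free and concerns the primary outcome. It does not invalidate the design.

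**What to change.** - State that region time series for the connectivity and graph analyses are extracted from unsmoothed normalised data, and that the 8 mm kernel is used for voxel-wise maps only.
- Take the hypothalamic mask from a source that contains the hypothalamus, in the same standard space as the other regions, and fix it before unmasking.

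The cost is a short documented amendment, for which the article already describes a route. No new data or participants are needed. Analysis begins only after data collection is complete and analysts are blinded to allocation, so the change can still be made blind. The downside is slightly noisier averages in small regions.
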